**a) Efficacy and exploratory outcome measures for the participant**		
The Addenbrooke's Cognitive Examination III^26^	Assesses cognitive function	Baseline/post-test
Everyday Cognition Questionnaire^27^	Measures everyday cognition in people with movement disorders	Baseline/post-test
Pill Questionnaire^37^	Measures functional capacity	Baseline/post-test
Lille Apathy Rating Scale^38^	A scale to detect and quantify apathy	Baseline/post-test
Relationship Satisfaction Scale^39^	Assesses level of satisfaction in a relationship	Baseline/post-test
The Brief Resilience Scale^40^	Assesses the ability to recover from stress	Baseline/post-test
Interpersonal Reactivity Index^41^	Measures empathetic concern	Baseline/post-test
Hospital Anxiety and Depression Scale^42^	Assesses depression and anxiety	Baseline/post-test
Parkinson's Disease Questionnaire-39^43^	A Parkinson's disease-specific quality of life measure	Baseline/post-test
Dementia Cognitive Fluctuation Scale^44^	Assesses proxy-reported fluctuations in cognition	Baseline/post-test
The Neuropsychiatric Inventory^45^	Assesses presence or absence of behavioural disturbances	Baseline/post-test
EuroQoL 5D^31^	Used for calculation of quality-adjusted life-years	Baseline/post-test
Client Services Receipt Inventory^30^	Collects information about medications and services used before entering the trial and during the trial	Baseline/post-test
**b) Exploratory outcome measures for the companion**		
Short Form-12 Health Survey^46^	Measures an individual's perception of their physical and mental health	Baseline/post-test
Relationship Satisfaction Scale^39^	Assesses level of satisfaction in a relationship	Baseline/post-test
Brief Resilience Scale^40^	Assesses the ability to recover from stress	Baseline/post-test
Hospital Anxiety and Depression Scale^42^	Assesses depression and anxiety	Baseline/post-test
Zarit Burden Interview^47^	Measures companion burden due to caregiving	Baseline/post-test
Dyadic Relationship Scale^48^	Measures positive and negative aspects of the dyadic relationship	Baseline/post-test
Relatives’ Stress Scale^49^	Measures perceived stress associated with caregiving	Baseline/post-test
Family caregiving role^50^	Measures aspects of caregiving related to satisfaction, love and anger	Baseline/post-test

Ascertaining efficacy of a complex intervention can be challenging since anticipating which outcome measures might be affected by the intervention as either a final or intermediate outcome (eg, mediators or moderators)^29^ can be difficult. Thus, we have carefully considered the underlying theoretical frameworks driving the process and consequently have incorporated several exploratory outcome variables to assist in determining what a clinically meaningful difference in the outcome might be (table 4). Data on exploratory outcome measures will be presented and summarised using means and SDs or alternatives in the case of non-normally distributed data. Data will be compared with previous trials of CST and iCST to understand the possible impact of the adapted therapy. This information can then be used to inform a subsequent full-scale hypothesis testing study designed to detect the smallest clinically meaningful difference.^23^

### Cost-effective analysis

To obtain data on the potential health economic and cost-effectiveness implications of the intervention in a subsequent fully powered RCT, we will assess the use of the Client Services Receipt Inventory^30^ and the EuroQoL 5D^31^ by using baseline and follow-up data to estimate the validity and responsiveness of these questionnaires.

### Adverse events

CST is not known to be associated with adverse events; however, we will monitor for such events. In the unlikely event that an adverse event occurs, the dyad will be directed to relevant health services, and the event will be recorded on a structured form. Advice on how to proceed (ie, to withdraw the dyad temporarily or permanently) with be sought from the chief investigator and sponsor.

## Ethics and dissemination

The trial has received favourable opinion from the research ethics’ committee (15/YH/0351). Protocol amendments will be prepared by the core research team as directed by the chief investigator and TSG. Ethical approval will be sought. The research governance offices and, where applicable, the trial registry, funding body and dyads will be informed of the trial amendments.

### Research governance

The trial is sponsored by the Greater Manchester Mental Health NHS Foundation Trust, UK. The TSG will provide operational management of the trial and supervision on behalf of the trial sponsor and the trial funder (National Institute for Health Research under the Research for Patient Benefit programme) to ensure that the trial is conducted as set out in the MRC's Guidelines for Good Clinical Practice. In this early phase trial, a formal data monitoring committee will not be convened; this function will be provided by the TSG. In relation to data monitoring, the TSG will safeguard the interests of trial dyads, assess the safety and efficacy of the intervention and make recommendations to stop the trial if warranted. The TSG will meet three times per year; terms of reference are available on request. There are no plans for interim analyses at this time.

### Dissemination policy

Findings will be submitted to high-impact peer-reviewed journals, presented at national international academic conferences and communicated to other universities. Publication authorship will be based on the International Committee of Medical Journal Editors’ criteria. Ongoing dissemination to clinicians and academics will be facilitated through the development and regular maintenance of a project-specific website. A lay summary will be sent to dyads (if requested) and presented at community engagement events.

### Summary

This mixed-methods protocol describes an early phase trial designed to primarily evaluate the feasibility and acceptability of CST-PD and whether there is sufficient evidence of clinical efficacy to justify a subsequent larger RCT. The protocol is congruent with the UK's MRC's updated guidance on ‘Developing and Evaluating Complex Interventions’^10^ and serves to enhance the design of a subsequent definitive large-scale trial.

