### Research questions and hypotheses

The following are research questions for the feasibility and exploratory study:Is it possible to recruit sufficient dyads in a timely manner?What is the acceptability and tolerability of the intervention by dyads?Which are the most clinically meaningful and acceptable outcomes by which to assess efficacy?Based on the findings, what would the sample size of a fully powered definitive RCT of the intervention be?

The following is the hypothesis to explore potential efficacy of the intervention:In people with PDD, MCI-PD or DLB, the change in cognitive function from baseline to withdrawal of CST-PD at 12 weeks will favour the intervention compared with treatment as usual (TAU).

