## Methods

This protocol was prepared in accordance with SPIRIT 2013 statement^12^ (checklist is available as an online supplementary file). The trial is registered with the ISRCNT (ISRCTN11455062); all study-related items from the WHO Trial Registration Data Set are available at the registry. The protocol lies within a research programme comprising a series of sequential steps in the development, feasibility testing, piloting and eventual full-scale trialling of a complex psychosocial intervention for people with PDD, MCI-PD or DLB. The programme has followed the UK's MRC's updated Guidance on ‘Developing and Evaluating Complex Interventions^10^ and is now at the feasibility, exploratory and pilot trial stage, which we describe here. Specifically, this part of the programme is a fully controlled randomised single-blind exploratory pilot trial with an embedded feasibility process evaluation and evaluation of new outcomes. The protocol for the process evaluation is not reported here but will form the basis of other papers. The pilot trial is designed and powered to test the hypothesis that CST-PD is superior to TAU for people with PDD, MCI-PD or DLB in improving cognitive function when assessed at baseline and 12 weeks post-randomisation. The therapy will be delivered in participants’ homes with recruiting sites in locations in Greater Manchester and other regions in the UK. A CONSORT-style flow chart for the trial is shown in figure 1.

10.1136/bmjopen-2017-016801.supp1Supplementary material 1

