### Sample size

A predetermined sample size for the feasibility aspects of this study is not required, since inferential statistics will only be exploratory. The sample size is determined by that required to detect a clinical meaningful difference in our primary outcome measure, cognitive function. To determine sample size, we referred to the previous literature^7 8 16^ and, taking a conservative approach, have estimated the standardised effect size on cognition of the parent form of the intervention to be 0.4. Thus, assuming 80% power and a correlation coefficient of 0.5 between baseline and endpoint on cognitive outcomes, the required sample size is 27 completers per group. By enrolling 32 dyads per group, it will allow for a 15% attrition rate (consistent with pilot sample guidance^17^). For the secondary, exploratory outcomes, the proposed sample size of 27 per group is within the recommended guidelines (24–50 participants^18 19^) required to estimate the standard deviation (SD) for a sample size calculation.

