#### Primary and exploratory outcome measures

The piloted efficacy and exploratory outcome measures for the participant are outlined in table 5a and the exploratory outcome measures for the companion in table 5b. The pilot efficacy measure on which the study has been powered is cognitive function as assessed using the Addenbrooke's Cognitive Examination III^26^ and the Everyday Cognition Questionnaire.^27^ Although the pilot trial has been powered on a previously reported effect size, the adaptation of the therapy and single outcome measure means that any potential treatment effects will be interpreted cautiously in order to not mislead the subsequent sample size and power calculation of the full RCT with multiple outcomes.^28^ With this caveat, we will test the hypothesis that compared with the TAU group, the difference in the total cognitive score between baseline and endpoint will be significantly greater in the experimental group. We will undertake a complete case analysis, only including trial completers without missing data, as well as an additional analysis based on last observation carried forward for dyads with missing data. Group differences in the change of outcome measures will be assessed using t-test or analysis of covariance adjusting for baseline differences, including cognitive stage at baseline.

**Table 5 T5:** Primary and exploratory outcome measures

Measure/author	Purpose	Time point

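### The article gives the efficacy result three different roles, and if the case for a larger trial is read from its significance test, 27 completers per group cannot support that use

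*Protocol article*

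**What the plan says.** The protocol article describes the role of the efficacy result differently in different sections.

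- **Objectives:** the primary objectives are operational feasibility and process evaluation. Efficacy on cognition is a secondary objective, worded as exploratory.
- **Background and rationale:** the small-scale trial is there to estimate the treatment effect and its variance.
- **Methods, opening paragraph:** "The pilot trial is designed and powered to test the hypothesis that CST-PD is superior to TAU". Table 1, the control-group section and the outcome section also describe the trial as powered on cognition.
- **Primary and exploratory outcome measures:** the hypothesis is that "the difference in the total cognitive score between baseline and endpoint will be significantly greater in the experimental group". The analysis is a t-test on change or ANCOVA. Treatment effects are to be interpreted cautiously, so that the sample size calculation for the full trial is not misled.
- **Summary:** beside feasibility and acceptability, the trial is to evaluate "whether there is sufficient evidence of clinical efficacy to justify a subsequent larger RCT".

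The planning figures are in Sample size. The authors "have estimated the standardised effect size on cognition of the parent form of the intervention to be 0.4" and, "assuming 80% power and a correlation coefficient of 0.5 between baseline and endpoint on cognitive outcomes", conclude that "the required sample size is 27 completers per group". They enrol 32 per group to allow for 15% attrition.

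**The concern.** A reader cannot tell from these sections what the efficacy result is for. Under the Objectives it is an exploratory estimate, and the decision to go on would rest on feasibility and process. Under the Summary it is part of the justification for the larger trial. The only yardstick the article attaches to efficacy is statistical significance.

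The two readings can give opposite conclusions from the same data. Recruitment, retention and delivery could all be good while the cognition test is non-significant. The Objectives would then support going on. The Summary, read together with the hypothesis test, might not.

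The repeated statement that the trial is powered makes this worse, because a reader told that power is 80% will take a null result as informative. The caution in the outcome section does not settle the matter: its stated purpose is to protect the next sample size calculation, and it does not say how a non-significant result bears on proceeding.

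**Working it through.** **Inputs.** From Sample size: standardised effect d = 0.4, baseline-endpoint correlation r = 0.5, 80% power, 27 completers per group, 32 enrolled. From the outcome section: t-test on change, or ANCOVA. Alpha and sidedness are not stated, so two-sided 5% is assumed and one-sided 5% is shown beside it. The effect is taken as a mean difference in units of the outcome SD.

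**Step 1: the plan's own figure.** The SD in standardised units is √(2(1 − r)) = √1.0 = 1.0 for a change score and √(1 − r²) = √0.75 = 0.866 for ANCOVA. The normal-approximation formula is n per group = 2(z_alpha + z_power)² SD² / d².

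- Two-sided 5%, change: 2 × (1.960 + 0.842)² × 1.0 / 0.16 = 98.1, so 99.
- Two-sided 5%, ANCOVA: 98.1 × 0.75 = 73.6, so 74.
- One-sided 5%: 78 (change) and 58 (ANCOVA).

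None is near 27. Getting close to 27 needs a choice the article does not state:

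- reading 0.4 as Cohen's f, that is d = 0.8 (26 per group by t-test);
- a repeated-measures group-by-time interaction with f = 0.2, which is a between-group difference in change of 0.8 SD (52 in total, 26 per group);
- ANCOVA at one-sided alpha 0.20 (27 exactly).

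The attrition step does reproduce: 27 / 0.85 = 31.8, so 32.

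**Step 2: what 27 per group delivers at d = 0.4.** The standard error is SD × √(2/27): 0.272 for change and 0.866 × 0.272 = 0.236 for ANCOVA. An observed 0.4 gives t = 0.4/0.272 = 1.47 (52 df) or 0.4/0.236 = 1.70 (51 df). The smallest significant observed effect is the critical t times the standard error. Power for a true 0.4 is from the noncentral t distribution.

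| 27 per group, r = 0.5 | Change score | ANCOVA |
|---|---|---|
| Two-sided p at observed 0.4 | 0.148 | 0.096 |
| One-sided p at observed 0.4 | 0.074 | 0.048 |
| 95% CI at observed 0.4 | −0.15 to 0.95 | −0.07 to 0.87 |
| Smallest significant effect, two-sided 5% | 0.55 | 0.47 |
| Smallest significant effect, one-sided 5% | 0.456 | 0.395 |
| Power at true 0.4, two-sided 5% | 30% | 38% |
| Power at true 0.4, one-sided 5% | 42% | 51% |

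The chance of a non-significant result when the true effect is 0.4 is therefore about 70% or 62% (two-sided), and 58% or 49% (one-sided).

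**Step 3: sensitivity.** If all 32 per group completed, the two-sided p at an observed 0.4 would be 0.115 (change) or 0.070 (ANCOVA), with power of 35% or 44%. At 27 per group and two-sided 5%, an observed 0.4 becomes significant by ANCOVA at r = 0.7 (p = 0.045) and on change at r = 0.8 (p = 0.024). The article's own r is 0.5.

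**Step 4: where the weakness comes from.** In a trial with 80% power for 0.4 at two-sided 5%, an observed 0.4 would sit at z = 1.960 + 0.842 = 2.80, clearly significant. The gap between 2.80 and the 1.47 or 1.70 above arises because 27 per group does not follow from the stated inputs.

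**The case against.** The strongest reply is that there is no significance gate. A reader might infer that an observed effect equal to the planned 0.4 would count against a larger trial. The article does not say so. It leaves sufficiency of evidence undefined in a one-sentence closing summary, and nowhere says that a non-significant result stops or weighs against the next trial. Several sections point the other way: Background and rationale speaks of estimating the effect, Overall aim of gathering design information, the research questions contain no efficacy go/no-go, and the outcome section promises caution. This stands, and the point is conditional for that reason.

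Second, a condensed article may leave progression criteria to the full protocol. That also stands, and the absence of such criteria is not raised here. What remains is that the article's own statements about the role of efficacy do not agree. Reading the Summary so that its emphasis falls on feasibility alone softens the clash, but efficacy still appears there as a justification for the larger trial, and Methods still calls the trial powered for superiority.

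Third, the hypothesis is directional and alpha is unstated, so it would be too strong to say flatly that 0.4 is non-significant. With one-sided 5% and ANCOVA it just passes (threshold 0.395), and the chance of missing a true 0.4 is then 49%, slightly under half. This stands as a limit on the numbers. It does not rescue 80% power under either analysis at one-sided or two-sided 5%.

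**Conclusion.** The point holds in conditional form. The article treats efficacy as a secondary exploration (Objectives), a powered superiority test (Methods) and part of the case for a larger trial (Summary), with significance as the only stated criterion. If sufficient evidence is judged by that test, a true effect of 0.4 would be detected about 30% to 38% of the time at two-sided 5%, or 42% to 51% at one-sided 5%, against the stated 80%.

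These figures rest on an assumed alpha of 5%, on 0.4 being a mean difference in outcome-SD units, and on the article's r of 0.5. If 0.4 was meant as Cohen's f, 27 per group is about right, but for a difference of 0.8 SD, twice what a reader would take from the text. The root cause is the sample size derivation. Correcting it alone would still leave the Objectives and the Summary in disagreement.

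**What to change.** 1. Align the opening of Methods, the outcome section and the Summary with the Objectives, so that feasibility and process are primary and cognition is secondary and exploratory throughout.
2. Correct the statements that the trial is powered on cognition, or restate the power that 27 completers per group give at 0.4, with alpha, sidedness, the scale of the effect and the analysis named.
3. Report cognition as the between-group difference with its 95% CI.
4. State in the Summary that a non-significant difference is not by itself grounds against a definitive trial.

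I would not add a rule that efficacy counts against proceeding only if the CI excludes 0.4. With half-widths of 0.546 (change) and 0.473 (ANCOVA), that needs an observed effect below 0.4 − 0.546 = −0.15 or 0.4 − 0.473 = −0.07, so the therapy would have to look worse than usual care first. In addition, 0.4 is the estimate for the parent therapy, not a stated minimum worthwhile effect.

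The cost is wording only, with no new data or visits. The trial gives up a headline efficacy claim.

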### Trial status

The INVEST study and trial started on 18 January 2016 and will be recruiting dyads from 1 March 2016 to 30 June 2017. The end date for data collection is 30 October 2017.

10.1136/bmjopen-2017-016801.supp2Supplementary material 2

10.1136/bmjopen-2017-016801.supp3Supplementary material 3

10.1136/bmjopen-2017-016801.supp4Supplementary material 4

10.1136/bmjopen-2017-016801.supp5Supplementary material 5

10.1136/bmjopen-2017-016801.supp6Supplementary material 6
